## Abstract

**Background:**

Compared to urban children, children living in rural areas of most countries, including China, are at higher risk of suffering unintentional injuries. Most proven injury prevention interventions, however, are rarely implemented in rural China due to lack of resources. Mobile health interventions are low-cost and easy-to-implement, facilitating implementing injury prevention in resource-limited areas (e.g., rural areas). This study is designed and implemented to examine the effectiveness of an app-based intervention for unintentional injury prevention among rural preschoolers in China.

**Methods:**

A single-blind, 18-month, parallel-group cluster randomized controlled trial with 1:1 allocation ratio will be implemented in 2 rural areas of China (Yang County, Shaanxi Province, and Shicheng County, Jiangxi Province). In total, at least 3508 rural caregivers of preschoolers aged 3–6 years old who own a smartphone will be recruited from 24 preschools. Clusters will be randomized at the preschool level and allocated to the control group (receiving routine school-based education plus app-based parenting education excluding unintentional injury prevention) or the intervention group (receiving routine school-based education plus app-based parenting education including unintentional injury prevention). External support strategies will be adopted by local partners to minimize user fatigue, non-compliance, and attrition. Data collection will be conducted at baseline and then every 3 months during the 18-month follow-up time period. Intention-to-treat data analysis will be implemented. Missing values will be imputed by using the Expectation Maximization algorithm. Generalized estimating equation will test the overall effectiveness of the app-based intervention. A per-protocol sensitivity analysis will be conducted to test the robustness of results. Subgroup analyses will follow the strategies for primary analyses. The primary outcome measure is the incidence rate of unintentional injury among preschoolers during the study period. Secondary outcome measures comprise longitudinal changes in caregiver’s attitudes, caregiver-reported supervision behaviors, and caregiver-assessed home environment safety surrounding child unintentional injury prevention in the last week using a standardized audit instrument.

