### Sample size

Based on previous literature [29], we conservatively hypothesize that the unintentional injury incidence of rural preschoolers aged 3–6 years old in project sites is 30% in the past 18 months. On the basis of a previous report [30], we assume the effect size of the app intervention to be 0.80 (incidence rate ratio) compared to traditional unintentional injury prevention intervention. In addition, we assume an intra-class correlation (ICC) of 0.005 with a cluster size of 150 children per preschool [31], and an allocation ratio of 1:1 between intervention and control groups. Considering extensive strategies will be adopted to increase retention in the study, we assume an attrition rate of 15% for the 18-month follow-up. Given these assumptions, a minimum sample size of 3508 caregivers is needed for the study to achieve a statistical power of 80% at the 0.05 significance level. As many rural preschools have more than 150 children in the study sites we select, 24 preschools will be ample to recruit the needed sample size.

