### Outcome measure

The primary outcome measure will be the incidence rate of unintentional injury among preschoolers in the past 18 months, which will be calculated by combining data from the six follow-up evaluations accumulatively. We will conduct follow-up evaluations on a quarterly basis (every 3 months) to reduce recall bias in participants remembering children’s minor or moderate injuries [24].

An injury event will be included if it meets any of three criteria [24]: (1) child receives a medical diagnosis or treatment by a doctor or other medical professional following an injury; (2) child receives first aid, takes any injury-related medication, or receives massage or cold/hot compress by a family member, teacher or other non-medical staff following an injury; or (3) child is restricted from school or other activities, or is kept in bed or rest for more than a half-day following an injury. If a caregiver reports that a child experienced more than one unintentional injury event in the past 3 months, we will record the number of injury events but collect specific information only about the most serious one.

Unintentional injury incidence rate will be calculated as “number of preschoolers newly experiencing unintentional injury events divided by total number of preschoolers×100%”.

We also will consider several secondary outcome measures, including: (1) the caregiver’s attitudes toward child unintentional injury prevention, (2) caregiver-reported supervision behaviors related to child unintentional injury prevention in the last week, and (3) the caregiver-reported home environment safety based on a standardized audit checklist over the last week. All secondary outcome measures are based on previously-published and validated items [24, 33–36]. Table 1 lists all planned survey items, with the final survey questionnaire to be refined through a pilot survey, as detailed below.

**Table 1 Tab1:** Survey items assessing child caregiver’s attitudes, supervising behaviors, and child home environment safety

**1. Caregiver’s attitudes** (with four response options: completely agree, partly agree, not sure, and completely disagree)	
a. Preventability of preschooler unintentional injury	
b. Self-efficacy to keep child safe from unintentional injury	
c. Necessity of preventing unintentional injury	
**2. Caregiver’s supervising behavior** (with five response options: always, often, seldom, never, and not applicable)	

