### Data analysis plan

Primary data analysis will follow an intention-to-treat (ITT) approach. Descriptive statistics will be calculated for socio-demographic variables and primary and secondary outcomes, including mean (or median) and standard deviation (or range and interquartile range) for continuous variables, and frequency and proportion for categorical variables. For each time point, Chi-square and two-sample *t*-tests (or Wilcoxon rank sum test if data are skewed) will be used to examine the differences in outcome measures between intervention and control groups for categorical and continuous variables, respectively. Trend tests or analysis of variance (ANOVA) will used to detect within-group differences across the six follow-up visits.

Generalized Estimating Equation (GEE) will be used to assess the overall effectiveness of the app-based intervention, while adjusting for socio-demographic variables, engagement, and baseline injury events.

A Generalized Linear Mixed Model (GLMM) will be used to verify the GEE results. With GLMM, missing values can be imputed using the Expectation Maximization (EM) algorithm. A per-protocol (PP) sensitivity analysis will be conducted to validate ITT results. All statistical analyses will be performed using R version 4.0.4. All statistical tests will be two-sided at the significance level of 0.05.

Subgroup analyses will be conducted to assess the impact of socio-demographic factors on the intervention effect, including gender and age of children and their caregivers, type of children’s caregivers (e.g., parents, grandparents, or others), education level of caregivers, and household income per capita per month. Subgroup analyses will employ the same statistical methods used for the primary analyses.

This study will strictly adhere to the Consolidated Standards of Reporting Trials (CONSORT) 2010 statement [37] and the Standard Protocol Items: Recommendations for Interventional Trials (SPIRIT) 2013 statement [38] to analyze the data and report the results.

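### The abstract and the analysis plan disagree on where EM imputation applies, and filling each gap once would ignore imputation uncertainty

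*Protocol article*

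**What the plan says.** The Methods part of the abstract states, without limit: "Missing values will be imputed by using the Expectation Maximization algorithm". The sentence stands between the intention-to-treat statement and the sentence that gives the GEE as the test of overall effectiveness.

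The Data analysis plan reads differently. It sets the population ("Primary data analysis will follow an intention-to-treat (ITT) approach") and the main model ("Generalized Estimating Equation (GEE) will be used to assess the overall effectiveness of the app-based intervention"), and attaches no missing-data method to that model. It then adds a second model: "A Generalized Linear Mixed Model (GLMM) will be used to verify the GEE results". EM appears only there, and only permissively: "With GLMM, missing values can be imputed using the Expectation Maximization (EM) algorithm".

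Two other sections show why this matters. Under Sample size, "we assume an attrition rate of 15% for the 18-month follow-up". Under Outcome measure, the primary outcome is the 18-month incidence, "which will be calculated by combining data from the six follow-up evaluations accumulatively". Neither place that names EM mentions repeated imputation, pooling, or any other step that carries imputation uncertainty into the standard error.

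**The concern.** There are two linked problems.

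First, the two statements cannot both govern the main test. On the abstract's wording, the GEE runs on data completed by EM. On the body's wording, EM belongs to the verifying model and the GEE has no stated method. An analysis plan written later could not follow both.

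Second, the named method is a poor choice if it is used as the word imputed suggests. EM gives one expected value for each gap. If that value enters the analysis as though it had been reported, the standard error treats predictions as data. The sample size is already inflated for 15% loss, so counting the lost children as observed would use the same information twice. At stake is the error rate of the main test on the abstract's reading, and of the check on it on the body's reading.

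**Working it through.** **Inputs.** From Sample size: control incidence 30%, ratio 0.80 (hence 24%, a difference of 6.0 points), ICC 0.005, 150 children per preschool, 15% attrition, total 3508, power 80%. From Preschool recruitment: 12 preschools per arm. From Data analysis plan: two-sided 0.05. Mean recruits per preschool: 3508 / 24 ≈ 146.

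**The plan's own figure.** Two proportions, 30% against 24%, need 855.5 (unpooled) or 859 (pooled) children per arm. The design effect is 1 + 149 × 0.005 = 1.745. Total = 2 × 855.5 × 1.745 / 0.85 = 3513, or 3527 pooled, against the stated 3508. The figure reproduces and already includes the 15% loss.

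**Why one fill narrows the standard error.** Let d = 0.15 be the share missing.
- *Fill with the arm mean.* Each preschool's deviation from its arm mean is multiplied by 1 − d, while the true sampling error of the arm mean is unchanged. The reported SE is then 1 − d = 0.85 of the true SE. A cluster-robust SE does not help, because the preschool deviations themselves have shrunk. The normal critical value becomes 1.96 × 0.85 = 1.67, a two-sided error of 9.6%.
- *Fill with a preschool-shrunken mean, as a mixed model would give.* About 146 × 0.85 = 124 children per preschool are observed. The weight on the preschool's own mean is w = 124 × 0.005 / (1 + 123 × 0.005) = 0.62 / 1.615 = 0.38. The SE ratio is 1 − 0.15 × (1 − 0.38) = 0.91. The critical value becomes 1.96 × 0.91 = 1.78, an error of about 7.5%.

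**Simulation.** 12 + 12 preschools of about 146, beta-binomial outcome, ICC 0.005, 15% lost completely at random, t test on 22 df. Where a range is given, it covers separate runs.

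| Handling of missing outcomes | Type I error | Mean difference (true 6.0) |
|---|---|---|
| Observed data, no fill | 5.1% | 5.99 |
| Arm-mean fill, whole outcome missing | 9.0% to 9.4% | 5.99 |
| One random draw within arm, whole outcome missing | 8.8% | 5.99 |
| Preschool-shrunken fill, whole outcome missing | 6.9% to 7.5% | – |
| Arm-mean fill, dropout spread over six quarters | 6.9% to 7.3% | – |
| Shrunken fill and dropout spread over six quarters | 6.3% to 6.4% | 6.0 |
| Own-preschool mean, cluster-robust SE | 5.1% | 5.99 |
| Fill from a model without arm, whole outcome missing | 5.1% | 5.09 |
| Multiple imputation, arm and preschool in model, 20 imputations | 4.6% | 5.99 |

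Power is 79.1% with observed data and 79.1% with multiple imputation. Arm-mean filling shows 86.6%, and that gain is spurious.

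**Dilution when the fill omits arm.** If the whole outcome is missing, the difference is 0.85 × 6.0 = 5.1 points. If dropout is spread evenly after 0 to 5 completed quarters at a constant hazard, the difference already observed at k quarters is 0.76^(k/6) − 0.70^(k/6), which averages 0.0283 over k = 0 to 5. Filling those not yet injured with the pooled 27% leaves 0.0283 × 0.73 = 0.0207 among leavers. The total is 0.051 + 0.15 × 0.0207 = 0.054, or 5.4 points.

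**The case against.** The best reply is that the body's sentence may be loose wording for likelihood estimation. EM is a standard way to obtain maximum-likelihood estimates in mixed models, and the body ties it to a GLMM, a model class for clustered, non-normal data. On that reading nothing is filled and no standard error shrinks. This is possible, but both places say imputed, so the wording would still need correcting.

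Several stronger readings are tempting, and the documents do not support them:

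- *That EM filling must either narrow the standard error or dilute the effect.* The own-preschool fill in the table did neither.
- *That the main result certainly rests on filled data.* Only the abstract implies this.
- *That at least 15% of children are affected.* The 15% is a planning assumption, not a minimum. The plan describes reminders and phone interviews, and a child who leaves early still contributes the completed quarters. At 5% missing, arm-mean filling gives a type I error of about 6%.
- *That a GEE on available cases is valid only under loss completely at random.* The planned GEE adjusts for covariates, and a correctly specified model tolerates loss that depends on them.
- *That the EM routine assumes normal, unclustered data.* No routine is named.

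It is also fair that this is a condensed article. The number of imputations and similar detail belong in an analysis plan, and their absence is no fault. The conflict between the two stated methods, and the choice of EM filling itself, remain.

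**Conclusion.** The concern stands in a limited form. The abstract and the Data analysis plan give different scopes for EM and must be reconciled. If EM supplies a single value per gap that is then analysed as observed, the type I error at 15% loss is about 6% to 9% rather than 5%. The upper end applies when the fill ignores preschool and the whole 18-month outcome is missing. The lower end applies when the fill uses preschool and dropout is spread over the quarters. A fill model that omits arm would keep the error rate near 5% but reduce the 6.0-point difference to about 5.1 to 5.4 points; nothing in the article says that arm would be omitted.

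These sizes assume loss completely at random, equal in both arms, and the plan's own incidence, ratio and ICC. On the abstract's reading the harm falls on the main test. On the body's reading it falls on the verifying GLMM, and the GEE has no stated method. This should be changed before analysis. It does not call the sample size into question.

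**What to change.** - Remove EM filling from both the abstract and the Data analysis plan, and state one method in the same terms in both.
- Fit the GLMM by maximum likelihood on all observed child-quarters, without imputing outcomes. This is valid when loss is at random given the observed data and the model is correctly specified.
- For the GEE, use multiple imputation suited to a binary or count outcome, with arm, preschool, visit and baseline covariates in the imputation model, pooled by Rubin's rules.
- A sensitivity analysis for loss not at random is optional.

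The cost is revised wording, a little more analysis work with standard R tools, no new data, and confidence intervals slightly wider than those from filled data. Under loss completely at random the simulated power equals that of the observed data (79.1%). The benefit of imputation over observed data would come where loss depends on earlier reports.

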**Discussion:**

The app-based intervention is expected to be feasible and effective over the 18-month intervention period. If the app is demonstrated effective as hypothesized, we will initiate processes to generalize and popularize it broadly to rural child caregivers across China.

**Trial registration:**

ChiCTR2000037606, registered on August 29, 2020.

## Background

Child unintentional injury continues to be a significant public health challenge in many countries worldwide, including China [1]. According to the Global Burden of Disease (GBD) study group 2019, approximately 38,000 Chinese children aged 0–14 years died from unintentional injury in 2019, and an additional 10,520,000 experienced unintentional injury events [2].

Various evidence-based child injury prevention interventions have been recommended by agencies such as the World Health Organization (WHO) and the United Nations International Children’s Emergency Fund (UNICEF), such as use of child restraints and seat-belts, child helmets, child-resistant containers, child safety locks, and smoke alarms [3]. However, these interventions are not consistently implemented in China, perhaps in part because no national agency has been assigned to coordinate national injury prevention efforts and promote the use of recommended interventions [4–6].

For a wide range of inequalities – including huge gaps in citizen safety awareness, adult supervision, injury prevention efforts, safety-related behavior patterns, health care services, as well as imbalanced and inadequate social-economic development between urban areas and rural areas [7–10] – children living in rural areas of China are significantly more likely to suffer an injury event than children living in urban areas consequently[11, 12]. The latest Chinese Disease Surveillance Points (DSP) data show that 2019 injury mortality rates in rural areas were significantly higher than in urban areas for under-1 children (21.56 vs. 14.55 per 100,000 population), children aged 1–4 years old (14.59 vs. 10.45 per 100,000 population), and children aged 5–14 years old (9.81 vs. 6.95 per 100,000 population) [13].

Traditional injury prevention programs require significant human, material, and financial resources to implement. Those resources are unavailable or limited in rural China. Mobile health (mHealth) interventions offer a solution that thoroughly overcomes many barriers of traditional interventions and have tremendous potential to deliver evidence-based interventions to rural citizens timely, broadly, conveniently, and efficiently, greatly boosting the accessibility and availability of health care services [14].

Successful delivery of mHealth interventions does require the recipients to have smartphones. According to *the 47th China Statistical Report on Internet Development* [15], the number of rural internet users has increased rapidly in China over the last decade, reaching 309 million by December 2020. Stated differently, internet penetration in rural areas of China has reached 55.9% and is anticipated to continue to grow rapidly [15]. This trend supports design and implementation of mHealth intervention programs for rural Chinese populations, including efforts to prevent child unintentional injury in rural areas of China.

Many mHealth interventions have been developed already for chronic disease management, maternal and infant health promotion, infectious disease prevention and control, and health services delivery [16–18], but our extensive literature searches find just 8 randomized controlled trials targeting child unintentional injury prevention via mHealth strategies [19–26]. This includes 4 trials in the United States, 1 in Australia, and 3 in China. All the eight programs were designed for urban children and implemented an intervention time interval of 8 months or less. Furthermore, seven trials used knowledge, attitudes, or behaviors as primary outcome measures to evaluate effectiveness rather than actual injury events. The only trial that examined actual changes in injury incidence rate used a 6-month intervention period and did not demonstrate the significant effectiveness [24]. User fatigue and resultant non-compliance to the intervention, plus substantial attrition from the study, were interpreted as reasons that the intervention was ineffective [27]. So far, the long-term effectiveness of mobile health technology in reducing actual child injury incidents has not been assessed in any published study.

We overcome all these limitations in the previously-proposed research. Specifically, we have refined and reinforced an app-based intervention that was previously designed and evaluated by our research team for unintentional injury prevention among caregivers of preschool children in urban Chinese areas [24]. The refinements overcome deficiencies revealed in the previous trial and meet specific needs of rural children and caregivers based on rural environment, injury spectrum of rural children, and characteristics of rural child caregivers comprehensively [28]. In this proposed research, the optimized app-based intervention will be conducted, and the sample monitored, for 18 months. We will use actual injury events as the primary outcome measure as well as considering participants’ attitudes, supervision behavior, and home environment safety. Sufficient external support from local cooperative partners will be implemented to rigorously minimize non-compliance and attrition. This study is the first mHealth randomized controlled trial (RCT) for caregivers of rural Chinese preschoolers to demonstrate the long-term effectiveness of preventing child unintentional injury via an app-based intervention and we hypothesize the innovative app-based intervention for 18 months will be effective in reducing child unintentional injury risk in rural China.

## Methods

### Study design

A single-blind, 18-month follow-up, parallel-group cluster randomized controlled trial with 1:1 allocation ratio will be implemented in Yang County, Shaanxi Province, and Shicheng County, Jiangxi Province, China. This trial was registered on August 29, 2020 in the Chinese Clinical Trial Registry (https://www.chictr.org.cn/showproj.aspx?proj=60036, registration number: ChiCTR2000037606).

### Sample size

Based on previous literature [29], we conservatively hypothesize that the unintentional injury incidence of rural preschoolers aged 3–6 years old in project sites is 30% in the past 18 months. On the basis of a previous report [30], we assume the effect size of the app intervention to be 0.80 (incidence rate ratio) compared to traditional unintentional injury prevention intervention. In addition, we assume an intra-class correlation (ICC) of 0.005 with a cluster size of 150 children per preschool [31], and an allocation ratio of 1:1 between intervention and control groups. Considering extensive strategies will be adopted to increase retention in the study, we assume an attrition rate of 15% for the 18-month follow-up. Given these assumptions, a minimum sample size of 3508 caregivers is needed for the study to achieve a statistical power of 80% at the 0.05 significance level. As many rural preschools have more than 150 children in the study sites we select, 24 preschools will be ample to recruit the needed sample size.

